#### Impact on PCC

To evaluate the impact of AI summarization on PCC, interviews with HCPs (n=10) will assess their perceptions of how the system influences their ability to provide PCC. These interviews will explore, when compared to a standard practice, if HCPs perceive an improvement in their capacity to understand patient priorities through the summaries, whether the summaries enhance their engagements and enable what they regard as more PCC outcomes, helped patients become active participants, and whether they felt they had the necessary skills to use the WMTY summaries [47].

#### Patient Benefit Measures

To evaluate the impact of the summarization tools on the quality and delivery of PCC, we will use multiple self-reported and validated measures, each capturing different aspects of potential patient benefit. Numerous tools are available for these purposes; however, the EQ-5D, collaBORATE tool, and Meaning in Life Questionnaire have been chosen as they are fast, reliable, and sensitive to changes over time. Two groups are needed to evaluate the impact: a control group (standard care without AI summaries) and an intervention group (care incorporating the AI-generated PCC summaries). Patients in both groups will be matched based on demographic and clinical characteristics to minimize confounding variables. Longitudinal assessments will occur at 3 time points: baseline, 1 month after intervention, and 6 months after intervention.

The EQ-5D is a standardized health-related quality-of-life measure that evaluates mobility, self-care, usual activities, pain or discomfort, and anxiety and depression [48]. The collaBORATE measure of patient-reported shared decision-making will help us evaluate how the AI-generated PC summaries facilitate the development of care plans aligned with patient values and preferences [49]. Finally, recognizing PCC involves developing personalized goals that produce health outcomes and improving a patient’s perception of meaning in life [21]. The Meaning in Life Questionnaire assesses the extent to which the AI system influences patients’ sense of meaning [50,51]. Patients in both groups will complete this questionnaire at baseline, 1 month, and 6 months postintervention.

A total of 100 participants will be recruited—50 (50%) participants in the control and 50 (50%) participants in the intervention group. Participants will be sourced from the 2 PCNs as in other stages of the study.

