Previous research and funding efforts have laid the groundwork for this proposal. We received support from the National Institute for Health and Care Research Invention for Innovation Funding At the Speed of Translation program to validate LLMs for generating automatic person-centered (PC) summaries of GP consultations [8]. Extensive engagement with patients and staff in 3 Plymouth practices and 1 Somerset GP practice informed our understanding that true PCC for this complex group of patients requires a better exchange of clinical and WMTY information into clinical records.

Our project proposes a feasibility study to co-design, collect, and analyze data to develop summarization models using an LLM to generate PC summaries of multiple primary and community service encounters among patients with frailty. Despite the good performance of current large language summarization models [7], implementation is challenging due to a lack of user engagement; ethical, legal, and data governance issues; and poor integration with existing data and workflows [9-11]. Importantly, intelligent data-driven care must also rely on unbalanced, missing, and incomplete clinical data drawn from imperfect real-world settings. Thus, careful preprocessing (eg, cleaning and substituting values) is essential to ensure good predictive modeling and prevent biases and unreliable outputs [12]. Our models, built on patients’ and key stakeholders’ preferences, values, and concerns, will be uniquely designed to generate interoperable PC summaries.

To this end, we will (1) engage stakeholders to understand technical, human factor, ethical, and regulatory barriers and enablers; (2) work with 2 primary care networks (PCNs) to audio record and transcribe primary and community encounters with 50 patients with frailty resulting in at least 150 audio-recorded conversations (eg, 3 encounters per patient); (3) develop and evaluate our LLMs ability to generate gold standard PC summaries that work for patients, carers, and MDT staff; (4) co-design implementation strategies and deploy pilot PC summary data into 2 PCNs; and (5) evaluate the summaries capacity to save HCPs’ time, improve PCC, and patient well-being.

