### Stage 3: Encounter Data Collection

Audio recordings of encounters between different members of an MDT team and patients with frailty will occur in 2 different PCNs, one between months 6 and 12 and another between months 9 and 15. The first PCN is more experienced in cross-team data sharing and deploying AI solutions and is more prepared to test the feasibility of audio recording encounters than the second PCN, which is more digitally immature. If necessary, access to these patient participants may also be supported by the Clinical Research Network Southwest Peninsula, which can assist the team in contacting other GPs who can help identify suitable and eligible research participants.

Working with GPs, we will identify 50 patients with frailty who require MDT engagement and ensure that MDT members know the project, its aims, methods, and data management protocols. To mitigate the limitations posed by our relatively small sample size, we will apply purposive stratification, ensuring a balanced representative sample across key frailty-associated factors, such as differing clinical frailty scores, typical comorbidity clusters, and social determinants.

To capture a patient’s data from multiple encounters between them and their community-based HCP, the research team will liaise closely with each patient participant and their community carers, encouraging them to provide updates on each future engagement over 2 months to record 3 to 5 consecutive encounters. Each patient will need to agree to participate in at least 3 encounters.

When the researcher is informed of an upcoming encounter, a consenting HCP or patient will notify the researcher of the time, date, and location. The researcher will then attend and record the conversation using high-quality audio-recording devices (Shure SM7B microphones). Patients will need an individual identifier to link encounter data from different MDT members and validate summarizations. Along with these identifiers, each encounter will be identified sequentially, from the first recording to the last. Each patient will participate in at least 3 encounters with HCPs (MDT members), resulting in approximately 150 conversations or encounters. All recordings (with anonymized identifiers) will be transcribed into text for concept design and model pretraining.

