After saturation, if stakeholder support for these model implementations exists, the research team will then work closely with the second focus group from stage 2, which includes local information governance specialists, IT services, data specialists, managers (hospital, primary care network, and care homes), local authorities, integrated care boards, and regional NHS regulatory boards (n=15). Across 3 sessions, this group will aim to create bespoke implementation strategies to reflect the 2 PCN systems’ infrastructure limitations, support teams’ specific needs embedding the models into daily practice, and deliberate methods of providing an ongoing support system for later pilot-testing and wider-scale deployment. In session 1, the group outlines a strategy to implement our system into their existing workflows and IT systems and identifies necessary adjustments to enable the model’s integration. Session 2 will ensure that the previous strategy meets regulatory and ethical guidelines, and finally, session 3 outlines a package of technical support and seeks to achieve agreement on responsibilities and channels for accessing this support channel and who provides the training.

After ensuring that both adopters and key stakeholder implementers are happy with the technology and that it could be implemented into their health systems, we will reach out to each clinical team engaged in its implementation, alongside local PCN technology deployment and support specialists, to finalize an agreed upon implementation and evaluation timeline and ensure they are happy with our proposed evaluation objectives and metrics (see stage 6 described subsequently). Once approved, we will engage each team and deliver essential training on using the system. This training will include preparing the microphone, recording, creating the PCC summary, sharing the summary in the electronic patient record, and building on past summaries with new clinical encounters for the same patient. Once all teams are happy with setting up, creating, sharing summaries, and accessing support, final verification of resources, allocation training, and support will be conducted, and then the AI system will go live.

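### Stage 6 attributes patient benefit to the tool from 50 v 50 matched groups in the two PCNs where it goes live, with the unit and mechanism of allocation not fixed

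*Protocol article*

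**What the plan says.** The Patient Benefit Measures section of Stage 6 sets up two concurrent groups: "a control group (standard care without AI summaries) and an intervention group (care incorporating the AI-generated PCC summaries". The size is fixed: "A total of 100 participants will be recruited—50 (50%) participants in the control and 50 (50%) participants in the intervention group". The one safeguard against confounding is that "Patients in both groups will be matched based on demographic and clinical characteristics to minimize confounding variables". Random allocation is mentioned nowhere in the article, and no rule says who or what decides which patients receive AI summaries. Outcomes are EQ-5D, collaboRATE and the Meaning in Life Questionnaire at baseline, 1 month and 6 months.

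On the source of patients, the section says: "Participants will be sourced from the 2 PCNs as in other stages of the study". The Background lists as an aim to "co-design implementation strategies and deploy pilot PC summary data into 2 PCNs". Stage 5 describes training team by team, then: "Once all teams are happy with setting up, creating, sharing summaries, and accessing support", there is a final check of resources "and then the AI system will go live". Stage 3 contrasts the sites: "The first PCN is more experienced in cross-team data sharing and deploying AI solutions", while the second is described as digitally less mature.

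On the inference, the Results section says that Stage 6 will clarify the patient and clinical benefits of the model, and the Abstract calls the expected insights into benefits and risks conclusive. For this comparison the Limitations section discusses sample size and generalizability. It does not mention selection, site or contamination.

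**The concern.** In a concurrent comparison without a stated chance mechanism, a difference can be attributed to the tool only if the groups are alike in everything else that affects the outcome. Matching on demographic and clinical characteristics deals with patient attributes. Three other influences are visible in the article itself:

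- **Site.** The PCNs differ in data sharing and experience with AI.
- **Team.** Training and go-live are organised by clinical team.
- **Willingness to be recorded.** The summaries depend on audio recording, and Stage 1 flags privacy worries about it.

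A difference in quality of life, shared decision-making or meaning in life could then arise from any of these. Equally, a real benefit could be diluted if controls are treated by staff who use the tool. At stake is the main patient-level claim of the evaluation.

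**Working it through.** **No figure to reproduce.** The article gives 50 per group without an effect size, SD, error rate, power or drop-out. Everything numerical below is an illustration on assumed inputs: two-sided 5% test, outcome scaled to SD 1, independent groups, no drop-out.

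**Step 1: what each possible split implies.**

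| Split of the arms | Compatible with the text? | Consequence |
|---|---|---|
| One PCN per arm | Not excluded | Arm and site are the same variable; no analysis separates them |
| Teams or practices within PCN | Not excluded | Team differences enter the contrast; contamination is limited |
| Patients within teams | Not excluded | Trained staff also treat controls |

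The first and third problems are largely alternatives. Which one applies depends on the level of allocation, which is not fixed. Matching on patient characteristics removes none of them.

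**Step 2: residual bias from selection or site.** Standard error of a difference = √(2/50) = 0.20 SD. With no true effect and bias b, the chance of a significant result is P(|Z + b/0.20| > 1.96).

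| b (SD, assumed) | b/0.20 | Rejection rate |
|---|---|---|
| 0 | 0 | 5% |
| 0.1 | 0.5 | 7.9% |
| 0.2 | 1.0 | 17.0% |
| 0.3 | 1.5 | 32.3% |

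If an analysis respecting the matching reduced the standard error, the same bias would weigh more, not less.

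**Step 3: contamination, if arms are split within teams.** If a fraction c of the effect also reaches controls, the contrast shrinks to d(1 − c). With assumed d = 0.5 and c = 0.3, it is 0.35. Power with 50 per arm falls from 71% to 42%, and the number per arm for 80% power rises from 63 to 129. This agrees with the inflation factor 1/(1 − 0.3)² = 2.04.

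**Step 4: one PCN per arm.** The design effect is 1 + 49 × ICC. An assumed ICC of 0.01, 0.02 or 0.05 gives 1.49, 1.98 or 3.45. A patient-level test that ignores this has a type I error of 2 × (1 − Φ(1.96/√design effect)) = 11%, 16% or 29%.

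**Step 5: claim against design.** The article promises clarification of patient benefit and conclusive insights, whereas its limitations for this comparison stop at sample size and generalizability. The claim goes further than matching alone can carry.

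**The case against.** The work is described as a feasibility and developmental study. Stage 6 happens only if Stage 5 succeeds, and the authors say that methods may need adapting and that larger studies should follow. A matched comparison is a defensible choice at that stage. This stands, and it lowers the severity; it does not support the strength of the benefit claims.

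Several stronger readings are tempting, and the documents do not support them:

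- **That PCN and baseline scores are left out of the matching.** The article gives no list of factors. A baseline EQ-5D score could count as clinical, and matching within PCN is not excluded. The list may sit in a fuller document.
- **That controls are patients who refused recording, had non-adopting teams or belong to the less mature PCN.** No passage says how a patient becomes a control, and go-live waits until all teams are content. These are possible routes only.
- **That site confounding and contamination both operate in full.** They are largely alternatives.
- **That controls have no follow-up schedule.** The article says both groups complete assessments at baseline, 1 month and 6 months. The exact anchor date and the analysis model are details that an article may leave to the full protocol or SAP.
- **That randomising patients would settle everything.** With team-level go-live and summaries shared in the patient record, patient-level allocation leaves the spill-over priced in Step 3.

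The numbers are also generic: they would apply to any non-randomised 50 v 50 comparison with such a bias. They show sensitivity and do not estimate the bias here.

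**Conclusion.** The point holds as one about allocation and attribution, and it should be fixed before ethics submission. Followed as written, the comparison does not allow a difference to be credited to the tool: matching on patient characteristics is the only stated control, both groups come from the two PCNs where the tool is deployed, and those PCNs differ by the article's own account. That the groups are not randomised is inferred from the matching sentence and the absence of any mention of randomisation.

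The direction and size of any bias are unknown. On the labelled assumptions, 0.1 to 0.3 SD of residual bias gives a false-positive rate of 8% to 32% instead of 5%. A reader might conclude that the question of patient benefit cannot be answered at all. That goes too far: a matched comparison can give exploratory evidence, but not the conclusive evidence that the Abstract promises.

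**What to change.** Replace the matching sentence with text that does the following:

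1. States the unit and mechanism of allocation.
2. Balances both arms within each PCN, preferably by random allocation: of patients, or of teams or practices within PCN where numbers allow, with clustering in the analysis.
3. Obtains agreement to recording from all patients before allocation.
4. Estimates differences adjusted for PCN and for the baseline score already collected. At an assumed baseline correlation r of 0.5 to 0.7, this cuts variance by r² = 25% to 49%.
5. Records control patients' exposure to professionals who use the tool.

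If randomisation is not feasible, match within PCN and on baseline score and willingness to be recorded, label the patient-benefit comparison exploratory, withdraw the word conclusive, and add selection, site and contamination to the limitations.

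**Cost.** Mainly wording plus a little more allocation and analysis work; the study has not yet gone to an ethics committee. The choice of unit is a trade-off. Patient-level allocation leaves some spill-over. Team-level allocation loses precision: with an assumed 10 patients per team and ICC of 0.01 to 0.05, the design effect is 1 + 9 × ICC = 1.09 to 1.45, and power at d = 0.5 falls from 71% to between 67% and 55%. The exploratory route costs a more modest claim.

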#### Risks

Participants’ well-being will be prioritized with minimal risks through careful study design and continuous monitoring. Participants can contact the principal investigator or data protection team with any data collection concerns. Interviews are scheduled to last 40 to 60 minutes, with focus groups lasting between 60 and 120 minutes. Recognizing that these time lengths may be demanding for older people and busy frontline clinicians, we implement the following mitigation strategies: provide flexible scheduling to minimize disruption; clear objectives and structured questions to make discussion efficient; offer frequent breaks to reduce fatigue, allowing people to step away if necessary; and provide options for remote participation. The facilitator will also continuously monitor participants during the session and be prepared to pause or end the session if fatigue is noticed. All interviews and focus groups will be conducted in private rooms to ensure privacy.

This research focuses on co-designing our AI models for end users, ensuring functionality and acceptability of audio recording clinical encounters to patients, clinicians, and health systems, and ensuring that these devices ethically and safely share data across an MDT. Consequently, the interviews avoid areas of cultural and psychological sensitivity and are low risk. We also expect that MDT members and hospital managers will have full ability to understand and consent, given their professional involvement in the program, its implementation, and associated improvements.

However, the participant pool will involve an older adult population, often with multimorbidity conditions, including dementia, learning disability, or mental health issues. Therefore, additional protection will ensure their safety and comfort, such as providing breaks and a supportive environment. In distress, participants will be directed to appropriate support services such as the Samaritans. The researcher will also follow a careful protocol to assess capacity to make decisions in line with the Mental Capacity Act 2005, which states that “a person must be assumed to have capacity unless it is established that he or she lacks capacity.”

Patients and staff may also disclose risks to themselves or others, such as professional malpractice and complaint issues. Thus, the research team will be updated with their mandatory safeguarding training. They will also have completed a Disclosure and Barring Service check before working with study participants. Using honorary NHS contracts, the research will also use NHS email accounts to ensure confidentiality and security when conveying sensitive material or collected data. They will also have a policy in place should the researchers become aware of any risks, safety issues, or concerns (ie, self-injury or suicidality) during interviews or focus groups. This escalation policy is taken from Devon’s Safeguarding Adults Partnership.

### Study Governance

A research ethics committee will review the study, and the team will obtain approval from the Health Research Authority through the Integrated Research Application System to protect participants’ rights, safety, dignity, and well-being.

A research management group will oversee the research. The research management group will be a learning partnership between 2 NHS integrated care boards, their subsidiary PCNs, and the university. This partnership group will oversee the delivery and direction of the research and meet regularly (bimonthly, every 2 weeks). Its membership will include a GP from each PCN, a deputy director of innovation and transformation, a chief clinical information officer, and senior researchers at the university’s center for health technology. Distributing the leadership ensures commitment and buy-in from the 2 organizations and a true partnership initiative.

### Ethical Considerations

This project has not yet been submitted to an institutional review board or the NHS Research Ethics Committee.

#### Informed Consent

HCPs and other associated stakeholders (n=30), excluding patients and carers, will be approached initially via an appropriate email introduction for an interview or focus group. These stakeholders will be identified within the 2 PCNs previously discussed. Initial contact will likely be bridged via a collaborating GP or one of their administrative team members. The introductory email will clarify the study’s aims and objectives, the organization’s consent to participate, the voluntary nature of participation, and the date by which they can withdraw their contributions without providing reasons or facing any consequences.

A participating HCP will first approach older patients (n=50) from the 2 PCNs. Using the participant information leaflet, they will provide an overview of the research. If interest is shown, a team researcher will provide further details, including the purpose of the research, a participant information sheet, and a consent form. These sheets will be adapted to ensure readability for older people, breaking down the stages of co-design, recording encounters, and evaluation. The researcher will explain the participant information sheet, the importance of the participant’s input, data use, sources for further information or queries, and withdrawal options. After 24 hours, participants can ask additional questions and provide consent.

#### Data Management

The research team will comply with the Data Protection Act 2018 requirements regarding collecting, storing, processing, and disclosing personal information. Electronic personal data (eg, consent forms) will only be stored on the university’s mainframe computer network, which is secure and password-protected. Paper copies of personal data will be destroyed using the university’s confidential waste management service. Each participant will be given a unique ID number that will be kept separate at the first stage of data storage. The key to IDs will be held in a safe and password-protected file on the university’s secure main computer drive. This password will not be shared with anyone except the principal investigator and their research assistant. The local custodian of the data will be the principal investigator at the university. In line with current recommendations around NHS-based research, all personal data are destroyed 3 months after the study’s completion.

Audio-recorded interviews and clinical encounters will be stored securely on PCN services and computers. The research team will transcribe all audio recordings, and all data will be pseudonymized. All audio-recorded conversations will be anonymized using Adobe Audition audio-editing software to silence location names and alter the voice’s pitch. Once anonymized encounters are transferred securely to the university’s OneDrive database on password-protected, encrypted university laptops. Subsequently, anonymized clinical encounters will be shared with the research team (n=4) and inputted into the AI model (n=150). No confidential or patient-identifiable data will leave an NHS setting at any stage.

Similarly, data related to developing and training LLMs will be stored securely on the university’s secure encrypted servers, including model configurations, training data, and evaluation metrics. Safeguards will be in place to ensure the integrity and confidentiality of the modeling data following institutional data security policies. In line with current recommendations around NHS-based research, this research data will be retained for 5 years after the study. After this, it will be archived in the university’s electronic archive and research repository and another suitable national or international data repository for long-term curation.

